### Safety

As the intervention is a simple exercise and not an untested drug or medical device, we do not expect any adverse events to occur. During each exercise, the subject’s heart rate will be monitored; when the heart rate reaches 80% of the heart rate reserve, the exercise will be stopped. After each training session, the subjects will complete the RPE scale, and the exercise intensity will be comprehensively controlled using the heart rate and RPE scale. Adverse effects such as dizziness, fainting, dyspnea, falls, or loss of consciousness during the intervention will be recorded and evaluated by the researchers to determine the relationship between the adverse event and the exercise program. We will use non-systematic approaches to collect the occurrence of adverse events. Subjects will also be encouraged to report any physical discomfort that they might experience during the exercise intervention. All adverse events will be recorded. If a direct injury occurs in connection with this study, the investigator will take appropriate medical treatment and provide basic rehabilitation treatment. In the event of a serious adverse event, the program will be terminated immediately; the investigators will record the event and report it in a trial application to the ethics committee within 24 h.

An oversight committee including a steering committee and a data monitoring committee will be formed. The monitors will include a statistician, a clinical trial scientist, and a physician with a medical background. The statistician will verify and validate the trial data, and the clinical trial scientist will monitor the progress of the trial on a regular basis so that the clinical trial is conducted in strict accordance with the trial protocol. The physician will regularly evaluate the safety and efficacy of the clinical trial progress to ensure that the rights of the subjects in the clinical trial are effectively protected. Moreover, auditors, who are completely independent of the clinical trials, will conduct monthly audits of the raw data, interventions, and clinical trials. If protocol modifications are required during the study, the modified protocol will be submitted to the Ethics Committee of the Shanghai Sports Institute for approval before implementation. Furthermore, no subgroup analysis with mid-term analysis is planned for this study.

No consent is required for the collection of participant information with biospecimens as we will not collect any biospecimens and do not intend to use the subjects’ data in future studies.

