**Discussion:**

This study will assess the effects of different conditioning methods of TCHE on lung function in middle-aged and elderly people. The final findings of this study will validate the effectiveness and safety of TCHE on lung function interventions in middle-aged and elderly people.

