### Strategies to improve adherence to interventions

Subjects will not be able to change their group during the intervention. To better monitor the subject’s skill practice, all exercises will be conducted under the guidance of a coach in the designated venue until the end of the 6-month intervention. The coach will monitor the attendance before each exercise, and the researchers will conduct telephone follow-ups. In the first 1–2 weeks, the main task will be to learn the movements with the explanation and demonstration of the coaches. Between weeks 3 and 6, the main task will be to improve the standardization of the movements. The coaches will further correct the movements based on the subjects’ basic mastery of the movement structure and strengthen the interaction between different movements. Between weeks 7 and 24, the main task will be to practice repeatedly to increase the subject’s understanding of the action.

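### The abstract promises to validate safety, but adverse events are collected non-systematically, with prompts worded around exercise and no equivalent query described for controls

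*Protocol article*

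**What the plan says.** In the abstract, the Discussion paragraph states that the findings "will validate the effectiveness and safety of TCHE on lung function interventions in middle-aged and elderly people".

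The Safety section of the Methods then describes how adverse events reach the record:

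- Method: "We will use non-systematic approaches to collect the occurrence of adverse events".
- Events named: "Adverse effects such as dizziness, fainting, dyspnea, falls, or loss of consciousness during the intervention will be recorded and evaluated by the researchers". The researchers judge how each relates to the exercise program.
- Self-report: "Subjects will also be encouraged to report any physical discomfort that they might experience during the exercise intervention".
- General statement: "All adverse events will be recorded".

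The section opens by saying that no adverse events are expected. It also provides for a physician who reviews safety regularly and for reporting of serious events to the ethics committee within 24 hours.

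Under Control group, what is recorded during the intervention period is exercise time and physical labor; no adverse-event question is mentioned. Under Strategies to improve adherence to interventions, a coach leads every session and "the researchers will conduct telephone follow-ups". The article does not say whether those calls ask about adverse events or whether they reach controls. All arms are tested at baseline, 3 months and 6 months (Trial design; Outcomes).

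**The concern.** A conclusion about safety needs a count of events that is reasonably complete. If arms are to be set against each other, it also needs a count obtained in the same way in each arm. The plan as worded secures neither. Non-systematic collection depends on someone volunteering or noticing an event. The only prompt described refers to exercise, which controls do not receive.

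Two errors could follow, and they run in opposite directions. In absolute terms, a low count in the exercise arms may partly reflect how events were collected, so exercise looks safer than it is. Relative to controls, closer observation of exercisers may make exercise look worse than it is. Later analysis cannot recover events that nobody asked about, so a separate statistical analysis plan would not cure this.

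**Working it through.** **1. The plan's own figure.** The only design figure that bears on the precision of the safety data is the sample size. Inputs from Sample size calculation: SD 48, SD of the means 8.16, alpha 0.05, power 80%, dropout 20%, four groups.

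- Effect size f = 8.16 / 48 = 0.17.
- Noncentral F, one-way ANOVA: 96 per group gives power 0.803.
- Allowing for dropout: 96 / (1 − 0.20) = 120 per group.

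The stated 120 is reproduced. It was set for FVC, not for safety.

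**2. What zero reported events would exclude.** Let n be the number of people and p the true proportion with at least one event. With complete capture, the one-sided 95% upper limit solves (1 − p)^n = 0.05, so p = 1 − 0.05^(1/n).

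**3. The same under incomplete capture.** If each affected person is recorded with probability c, then (1 − cp)^n = 0.05, so p = [1 − 0.05^(1/n)] / c. The documents give no value for c; 0.50 and 0.25 are assumptions that show a range.

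| Group | n | c = 1 | c = 0.50 (assumed) | c = 0.25 (assumed) |
|---|---|---|---|---|
| One arm | 120 | 2.47% | 2.47 / 0.50 = 4.9% | 2.47 / 0.25 = 9.9% |
| Three exercise arms | 360 | 0.83% | 0.83 / 0.50 = 1.7% | 0.83 / 0.25 = 3.3% |

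The pooled row assumes one common rate in the three exercise arms. If only the expected completers contributed (96 per arm, 288 in the three arms), the complete-capture limits would be 3.07% and 1.03%.

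**4. Opportunity for capture by arm.** Exercise arms: 5 sessions a week over the 24 weeks of the teaching schedule is 5 × 24 = 120; over 26 weeks it is 5 × 26 = 130. Controls: no exercise sessions. They do receive health education, have their activity recorded, and attend the 3- and 6-month tests, but no adverse-event question is described at any of these contacts.

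**5. Effect on a naive comparison.** If true risk were equal in all arms and controls' events were captured at 75%, 50% or 25% of the exercise arms' rate (assumed), the apparent risk ratio of exercise to control would be 1/0.75 = 1.33, 1/0.50 = 2.0 or 1/0.25 = 4.0.

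**The case against.** Safety is not an objective of this trial. The stated purpose, the primary and secondary outcomes and the Statistical methods all concern lung function, and the promise about safety is one sentence in the abstract. Non-systematic collection is a legitimate choice for a descriptive list of events, and rewording that sentence would by itself remove the contradiction. This stands. It limits the weight of the point but does not dissolve it, because the sentence promises a finding that the stated method cannot deliver.

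The Safety section also says that all adverse events will be recorded. The phrase about events during the intervention can mean the whole 6 months; the adherence section uses it that way when it bars changes of group. Sessions are coach-led with heart-rate monitoring, so acute events in a session would probably be seen. This too stands in part. However, recording what is reported is not the same as asking, and physician review and rapid reporting act only on events that reach the record.

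Four stronger readings are tempting, and the documents do not support them:

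- *Controls have no route for reporting.* They have several contacts. What is missing is a described adverse-event question.
- *Events between sessions or after dropout are lost.* The text does not exclude them; it is ambiguous.
- *The trial will yield a false between-arm difference in adverse events.* Statistical methods plans no such comparison, so the ratios in step 5 show only what a reader might compute from the counts.
- *Unblinded judgement of causality is a further defect.* Relating an event to the exercise program requires knowing whether the person exercised, and the article states openly who is not blinded.

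Finally, the abstract's claim is about TCHE as a whole, so the pooled limit of 0.83% is as relevant as the single-arm 2.5%.

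**Conclusion.** The point holds as a mismatch between a stated conclusion and a stated method. The abstract promises validation of safety. The Safety section provides non-systematic collection with an exercise-worded prompt, and the article describes no equivalent query for controls. Capture is likely to be incomplete and unequal between arms, by an amount that the documents do not allow anyone to estimate.

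Zero reported events would exclude true rates above about 2.5% (one arm) or 0.83% (three exercise arms) only if capture were complete. At an assumed 50% capture both limits double. These limits are one-sided 95%, count people with at least one event, and treat people as independent.

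The change should be made, but it does not threaten the primary analysis of FVC, and safety is not a listed outcome.

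**What to change.** 1. Replace non-systematic collection with one short, fixed set of adverse-event questions, identical in all four arms, at the existing 3- and 6-month visits. Use the same questions in telephone follow-ups where these are already made. No new call schedule for controls is needed.
2. Have subjects complete the questions on a form, or have unblinded follow-up staff ask them, so that the answers do not unblind the outcome assessor.
3. Keep spontaneous and session reports as a separate listing. Tabulate the elicited events by randomised arm with exact confidence intervals.
4. Reword the abstract so that the trial will estimate the effect on lung function and describe reported adverse events, in place of validating effectiveness and safety.

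The cost is a one-page form, and more events, mostly minor, will be recorded. The article describes recruitment as still to begin, which is when this is easiest to change. If the collection method is kept as it is, item 4 alone still removes the contradiction, and the safety results should then be presented only as a list of reported events.

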### Data management and dissemination

Data will be recorded in pairs, outliers will be identified to avoid entry errors, and auditors will conduct regular spot checks to ensure the authenticity and accuracy of the data.

The data in this experiment, including subject identity and personal information, outcome indicator data, and other related data, will be kept strictly confidential. A list of the participants’ contact information and their corresponding ID numbers will be kept separately from the other data. All paper copy forms will be stored in locked filing cabinets during the test. At the end of the experiment, these files will be scanned and transferred to a password-protected computer. Only authorized research assistants will have access to the final trial dataset.

Upon completion of the trial, the Shanghai Sports Institute Clinical Research Service will be invited to report on the results. The results of the trial will be published in peer-reviewed journals and shared at relevant national and international conferences.

## Discussion

Physical exercise is an important factor that improves the health status of people of all ages [46], and lack of physical exercise is a leading cause of mortality worldwide [47]. Sports practice provides a wide range of health benefits, including the prevention of chronic illnesses and complications and improvement of postoperative recovery speed [13]; no other single intervention or treatment can produce such a wide range of benefits to health [48]. However, not all diseases can be effectively improved by exercise. Different types of diseases require different types of exercise for targeted interventions [13]. The types of exercise recommended in the lung rehabilitation guidelines include endurance, intermittent resistance, and flexibility training [15]. Endurance training is the main component of the lung rehabilitation exercise plan, but its intervention effect is more significant when performed in combination with other types of exercises [49]. In terms of intensity, the evidence suggests that moderate exercise intensity plays an essential role in health [50]. TCHE is a type of moderate exercise intensity and is considered a safe method of exercise and medical treatment [18, 51]. Furthermore, the use of traditional lung rehabilitation therapy is limited worldwide due to funding, technology, resources, and other conditions [15]. However, TCHEs are more accessible in terms of venue, equipment, cost, and other objective conditions compared with traditional lung rehabilitation therapy [20]. Furthermore, TCHE can function as a means to prevent and treat various chronic diseases, making them a viable alternative to lung rehabilitation therapy.

TCHEs have both direct and indirect impacts on lung functioning. Indirectly, they have a positive effect on lung function by influencing other factors including body mass index (BMI), waist circumference, blood glucose, blood lipid, and blood pressure levels [52]. A previous study found that the TCHEs improve blood pressure [53], BMI [54, 55], waist circumference [55], blood sugar [56], and other variables. Additionally, TCHEs significantly improve depression, anxiety, and sleep quality [57–59]. To explore the different effects of different conditioning methods on the lung function of healthy middle-aged and elderly people, this study distinguishes the different technical movements according to the different conditioning methods. This distinction does not represent a separate relationship between “breath regulation,” “body regulation,” and “heart regulation”; rather, it focuses on the same conditioning methods for integration. Additionally, although these three conditioning methods improve lung function, they differ somewhat in their mechanisms.

This study has some limitations. First, due to the restrictions of the exercise intervention, it is impossible to blind the subjects and coaches, which may cause a certain risk of bias. Because of the nature of the exercise intervention, subjects will know whether they belong to the intervention or control group, which may increase the variability of the intervention in terms of psychological and physiological differences, and in addition may increase the likelihood that the control group will seek to perform the exercise intervention. Additionally, the differences in cultural background and medical environment may also limit the promotion and applicability of TCHEs in other countries and regions. Considering that the intervention could easily be interrupted due to the COVID-19 pandemic, we had to postpone the formal recruitment of subjects. After consulting with relevant experts, we made appropriate modifications and refinements to this protocol.

This paper introduces the design of a clinical trial, which aims to study the effect of different conditioning methods of TCHEs on the lung function of healthy middle-aged and elderly people. Through a comparative analysis of different conditioning methods on the improvement of lung function, this protocol aims to explore the conditioning methods that are more conducive to promoting the improvement of lung function in healthy middle-aged and elderly people and can provide a reference for more targeted exercise prescriptions to improve lung function.

## Trial status

The recruitment of subjects is expected to begin on March 1, 2022, and the study is expected to end on July 1, 2024.

## Data Availability

The datasets used or analyzed in the study can be obtained from the corresponding author upon completion of the study.

## Abbreviations

ANOVA: Analysis of variance
ATS/ERS: American Thoracic Association/European Respiratory Association
BMI: Body mass index
COPD: Chronic obstructive pulmonary disease
FEV1: Forced expiratory volume in 1 s
FVC: Forced vital capacity
MCID: Minimum clinically significant difference
MVV: Maximal voluntary ventilation
RPE: Ratings of perceived exertion
SD: Standard deviation
TCHE: Traditional Chinese health exercise
VC: Vital capacity
